**SUMMARY**

**Justification of the study**

According to recent estimates, nearly one billion people still suffer from hunger. Malnutrition remains a major cause of morbidity and maternal and infant mortality in sub-Saharan Africa (FAO, 2010). Malnutrition includes chronic and acute forms, as well as deficits in essential micronutrients. Access to a rich and good quality diet remains difficult for many people. Poor households continue to have a diet low in diversity and poor in foods with essential micronutrients such as vitamin A, iron and zinc (Arimond, 2010). Iron deficiency in its most severe form leads to anemia. In Senegal, nearly 83% of children 12-23 months olds are anemic and 64.5% of children of the same age have an iron deficiency (MI, 2012).

In 2006, the Laiterie du Berger (LDB) began collecting milk from herding families living in the area of Richard Toll, in the Senegal River Valley. The originality of LDB is that it produces yogurt by collecting fresh milk twice a day in households situated within a 50 km radius around the factory. Over the years, LDB has developed a network of 700 suppliers on 4 main collection routes. However, during the dry season, LDB is faced with a significant drop in volumes and collections face great irregularity. One of the hypotheses brought forward to explain this phenomenon is that those who collect the milk (women, children, herders) are not always those who receive the payments. Another possibility is the sale of milk at markets in the dry season can fetch a higher price than that fixed by LDB.

This study aims to test a type of incentive among farmers so that they might provide milk to LDB more regularly during the dry season. The incentive will be distributed as a bonus, after agreeing upon a contract, with a target volume (corresponding to 1 liter of milk per lactating cow per day) and regularity in the frequency of milk collection, at the beginning of the dry season. The incentive tested will be a bonus dairy product produced by LDB itself: fortified Thiakry. This form of incentive corresponds to the "Value Chain" concept: the initial product is the milk produced by herders and the processing of the milk produces yogurt, to which millet and fortification are added. This results in a final product (fortified Thiakry) that will be returned to herders and has a value added compared to the initial product.

**Methodology**

**1. Overall objective, specific objectives, type of study, and number of subjects**

*Overall objective:* to demonstrate the "Value Chain" concept in a contractual agreement linking the Laiterie du Berger and milk producers in the area of Richard Toll, Senegal.

*Specific objectives:* to compare the results of a fortified Thiakry intervention versus a control group, concerning:
- Increasing the volume of milk and the frequency of collection during the dry season
- Reducing the prevalence of anemia among children aged 2 to 5 years

*Type of study:* cluster randomized control trial, comparing households receiving fortified (with iron) Thiakry to control households receiving no intervention. Children 2 to 5 years at baseline will be visited 6 months and 1 year from the beginning of the study.

*Number of required subjects:* 700 families of herders in total.

**2. Criteria for assessment**

*Main outcome of the intervention:* proportion of herders who have reached the objective defined at the beginning of study in the contract with LDB, in terms of volume and collection frequency for milk over the duration of the study

*Main outcome for the "Nutrition" component of the intervention*: proportion of children 2 to 5 years presenting severe, moderate, and mild anemia (defined thresholds respectively are <7, between 7 and 9.9, and between 10 and 10.9 g/dl of hemoglobin).

*Secondary outcomes of the "Nutrition" component (at 6 and 12 months of follow-up):*
- Mean level of hemoglobin (in g/dl)
- Proportion of children 2 to 5 suffering from stunting (Height-for-Age Indices <-2SD)
- Proportion of children 2 to 5 years suffering from acute malnutrition (Weight-for-Height Indices <-2 SD)
- Proportion of children 2 to 5 years who are underweight (Weight-for-Age Indices <-2 SD)
- 24 hour food consumption diversity (qualitative)

- Household food consumption over 7 days (consumption frequency of different food groups)

**3. Selection Criteria**

All households of herders supplying milk to the Laiterie du Berger and having children 2 to 5 years in the household, who agree to participate in the study

**4. Trial Procedures**

- An information-sharing meeting will be held on each collection route, gathering all the heads of households to: explain the terms of the study and the targets to achieve in terms of milk collection; perform the intervention lottery to define the treatment and control groups; distribute the explanatory note of the study and the information sheet on anemia (in French and Fulani); and distribute a form indicating willingness to participate in the study (to be brought, signed, to a second meeting 10 days later)
- An awareness-raising campaign will be implemented in the study zone by the Cellule de Lutte contre la Malnutrition (Unit for the Fight against Malnutrition; CLM) in January 2013, through community representatives of ASBEF in villages and through radio commercials, in order to inform mothers on good feeding practices and explain the problems of anemia. This campaign will take place in the study zone for 6 months.
- A first household survey will take place in January 2013, to gather baseline data through the form of a household questionnaire (household composition, herding/cow data, socio-economic data, household consumption etc.); anthropometric data; and hemoglobin measures of children 6 months to 5 years old and their mothers, using HemoCue®.

- A distribution phase of incentives (fortified Thiakry) for 6 months, from January 2013 to July 2013.
- A second phase of data collection in July 2013, through household questionnaire and measurement of hemoglobin levels as during the baseline data collection.
- A third phase of data collection in January 2014, through household questionnaire and measurement of hemoglobin levels.

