# 2. Objectives of the study

*Overall objective:* to demonstrate the "Value Chain" concept in a contractual agreement linking the Laiterie du Berger and milk producers in the area of Richard Toll, Senegal.

*Specific objectives:* to compare the results of a micronutrient-fortified Thiakry intervention with a control group, specifically concerning:
- Increasing the volume of milk and the frequency of collection during the dry season
- Reducing the prevalence of anemia among children aged 2 to 5 years

3. Criteria for assessment

*Main outcome of the intervention:* proportion of herders who have reached their contract objective defined in the beginning of study, in terms of volume and collection frequency for milk over the duration of the study

*Main outcome for the "Nutrition" component:* proportion of children 2 to 5 years presentingsevere, moderate, and mild anemia (defined thresholds respectively are <7, between 7 and 9.9, and between 10 and 10.9 g/dl of hemoglobin).

*Secondary outcome of the "Nutrition" component (at 6 and 12 months of follow-up):*- Mean level of hemoglobin (in g/dl)
- Proportion of children 2 to 5 suffering from stunting (Height-for-Age Indices <-2SD)
- Proportion of children 2 to 5 years suffering from acute malnutrition (Weight-for-Height Indices <-2 SD)
- Proportion of children 2 to 5 years who are underweight (Weight-for-Age Indices <-2 SD)

- Household food consumption

- Children’s dietary diversity

*Definitions:*

- Mild anemia in children: level of hemoglobin between 10 and 10.9 g/dl of blood

- Moderate anemia in children: level of hemoglobin between 7 and 9.9 g/dl of blood

- Severe anemia in children: level of hemoglobin less than 7 g/dl of blood

- Stunting (Height-for-Age Indices <-2SD)

- Acute malnutrition or wasting (Weight-for-Height Indices <-2 SD)

- Underweight (Weight-for-Age Indices <-2 SD)

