# 6. Subject characteristics

# *Selection Criteria:*

- All households of herders supplying milk to the Laiterie du Berger and having children 2 to 5 years in the household, who agree to regularly provide milk to LDB

- Signature of an agreement to participate in the study by the head of household and his/her spouse(s) and signature of the informed consent by the mother of the children

*Non-inclusion criteria:*

- Refusal to participate in the study

*Exclusion criteria:*

- Subjects may discontinue participation in the study at any moment

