# 8. Conditions of the lottery

The two groups will be chosen by lottery at the first information-sharing meeting. The draw will define the households receiving free fortified Thiakry for all children aged 2 to 5 years within their household (treatment group) and the households not receiving fortified Thiakry during the study (control group), who will receive in kind compensation at the end of the study as thanks for their participation.

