# 10. Test Procedures

**10.1.** **Information and study recruitment**

A meeting will be held along each milk collection route, gathering all heads of households, in order to explain:
- Causes and consequences of anemia and the fact that LDB will make available to herders fortified Thiakry that fights against anemia
- The terms of the study, which are:

- the objectives in terms of milk collection
- the lottery defining the two intervention groups: the households receiving free fortified Thiakry for all children aged 2 to 5 years in the household and the households receiving no incentive but having the opportunity to buy fortified Thiakry directly from LDB if they wish
- the number of data collection rounds by enumerators for households etc.

- That mothers and children will have a drop of blood collected (finger prick) to measure their hemoglobin levels. The results will be immediately available and provided to families. In cases of severe anemia in children, IFPRI will facilitate transportation and will cover the price of the consultation and the cost of treatment at the nearest health center.

Household heads will leave the information meeting with an explanatory note of the study (in French and Fulani) and a form of intent to participate in the study (in French and Fulani). The form must be returned, signed by the head of household and their spouse, at the second meeting 10 days later, which will be establish the milk collection targets (contracts with LDB).

When the enumerators go to the households to begin data collection, they will read a document covering all the important aspects of the study and will obtain signature on a two-part informed consent form, targeting the household heads and the mothers.

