**10.3. First household data collection (Baseline)**

An initial survey of households will take place in January 2013 to gather baseline data. The questionnaire, in Fulani, will collect data related to:
- Composition of the household
- Herding/cows (size of herd, etc.)
- Crops (crop type, etc.)
- Socioeconomic status (household goods, level of education, etc.)
- Household food consumption (frequency, food security, etc.)

Additionally, measurements of hemoglobin levels will be conducted for children 6 months to 5 years, as well as their mothers, by drawing a drop of blood using a lancet and placing it in a microcuvette, allowing a direct reading of the result using a HemoCue® Analyzer

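### The lottery is drawn before households agree, sign their milk contract or give consent, so known allocation can bias who enters each arm and could influence the commitment behind the main outcome

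*Protocol*

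**What the plan says.** The order of steps is given twice and consistently.

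- **Draw.** Section 8: "The two groups will be chosen by lottery at the first information-sharing meeting". Summary section 4 agrees, listing among the tasks of that meeting to "perform the intervention lottery to define the treatment and control groups".
- **Agreement.** At that same meeting the organisers only "distribute a form indicating willingness to participate in the study (to be brought, signed, to a second meeting 10 days later").
- **Contract.** Section 10.1 has the form returned "at the second meeting 10 days later, which will be establish the milk collection targets (contracts with LDB").
- **Consent.** When enumerators reach the household to begin data collection, they "will obtain signature on a two-part informed consent form, targeting the household heads and the mothers" (Section 10.1).
- **Baseline.** Section 10.3 on the first household data collection: "An initial survey of households will take place in January 2013 to gather baseline data".

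Two other provisions make this order matter. Section 6 admits only households "who agree to regularly provide milk to LDB" and that sign an agreement to participate. The main outcome is the "proportion of herders who have reached their contract objective defined in the beginning of study" (criteria for assessment, after Section 2).

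**The concern.** Random allocation protects a comparison when the set of units, and the yardstick for each, are fixed before anyone knows the arm. Here neither is.

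- **Entry.** A household that learns it is a control can decline to return the form, or decline consent, more or less readily than a treatment household. As worded, the main outcome exists only for households with a contract, so one that declines after the draw leaves the denominator. Section 11.1 specifies intent-to-treat only for the secondary variables, and only for children with hemoglobin results. Households lost between draw and consent fall outside that population too.
- **Commitment.** Under Section 10.4 a treatment herder who falls short receives a warning or loses the next week's product. A control herder faces neither. A modest commitment therefore has value in one arm only. Recruitment and random assignment (Section 12.1) and identification of the contract objectives (Summary section 5) lie with the same partner, so those settling the contracts are likely to know the arm.

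If either mechanism operated, a difference in contract achievement could not be attributed cleanly to the incentive.

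**Working it through.** **1. Sequence.** Set side by side, the steps are: lottery (first meeting), signed form and contract (second meeting, 10 days later), then consent and baseline data (household visit, January 2013). The meetings are not dated. That the draw precedes baseline follows from Section 10.1, where consent and data collection come after the meetings, and from the order of steps in Summary section 4. No section places agreement, contract, consent or baseline before the draw. The protocol states no figure for this risk, so there is none to reproduce.

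**2. Selective entry: illustration on assumed values.** Let P be the true share reaching the objective, d the share of an arm that declines after the draw, and s the share of decliners who would have succeeded. The share observed among entrants is

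(P − d·s) / (1 − d).

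Take P = 50% in both arms, so there is no true effect. All values of P, d and s are assumptions.

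| Decline, treatment / control | s | Treatment observed | Control observed | Treatment − control |
|---|---|---|---|---|
| 0% / 5% | 0 | 50.0% | 50/95 = 52.6% | −2.6 points |
| 0% / 15% | 0 | 50.0% | 50/85 = 58.8% | −8.8 points |
| 10% / 20% | 0 | 50/90 = 55.6% | 50/80 = 62.5% | −6.9 points |
| 5% / 25% | 0 | 50/95 = 52.6% | 50/75 = 66.7% | −14.0 points |
| 10% / 20% | 25% | 47.5/90 = 52.8% | 45/80 = 56.3% | −3.5 points |
| 5% / 25% | 25% | 48.75/95 = 51.3% | 43.75/75 = 58.3% | −7.0 points |

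The s = 0 rows assume that every decliner would have failed, so they are the worst case for those decline rates. With s = P the bias vanishes. With s above P, or with more refusal in the treatment arm, the sign reverses.

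Some non-participation is expected: Section 7 anticipates that not all households will take part. It allows one further 20% for this together with missed targets and incomplete consumption, and does not split it by arm, so it does not inform d.

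**3. Commitment: illustration on assumed values.** Suppose milk supplied relative to the proper target is normal with mean 1 and standard deviation SD, and one arm's target is a fraction x too low. That arm's success share is then Φ(x/SD), against 50% in the other arm. With x = 5% and SD = 0.3 it is Φ(0.17) = 57%. With x = 20% and SD = 0.2 it is Φ(1) = 84%. No document figure supports any x other than zero. The calculation shows only that a threshold outcome is sensitive to where the threshold sits. If targets were lowered in the treatment arm, the bias would run opposite to that in step 2.

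**The case against.** There is a good case that the risk is contained.

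- **The target is largely rule-bound.** The volume target is 1 litre per lactating cow per day for everyone, and the milk objectives are explained at the first meeting. No section says when cows are counted, or that the herder declares the count himself. The baseline questionnaire also collects herd data. A reader might infer that each arm is in fact held to a different bar; the documents do not support that. What stands is narrower: individual contracts are settled after allocation, so the cow count used and the regularity agreed could still be influenced by the arm.
- **Controls have reasons to join.** They receive in-kind compensation at the end (Section 8), immediate hemoglobin results, paid care for severe anemia and the option to buy the product (Section 10.1), and deworming for included children (Section 10.3 on helminths). They face no warning or loss of product. Lower uptake among controls is therefore plausible, not certain.
- **Adjustment is planned.** Sections 11.1 and 11.2 provide baseline comparison, covariate adjustment, difference in differences for anemia and hemoglobin, and an optional propensity score. It would be wrong to say these fail because selection happens before baseline: imbalance in measured characteristics is what they can partly capture. They cannot correct unmeasured selection, recover households never surveyed, or repair a target fixed after allocation.
- **Enumerators are blinded as far as possible** (Section 11.4). This limits measurement bias but has no bearing on entry or contract setting.

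A separate analysis plan would not answer the point, because analysis cannot change the order of enrolment.

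**Conclusion.** The concern holds as a risk built into the design. Following the protocol as written, households enter, and settle their contracts, knowing their arm, and the main outcome depends on both steps. The safeguards reduce the exposure without closing it.

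Size and direction are unknown. With an assumed 50% true rate in both arms, and decliners who would all have failed, selective entry gives a false difference of about 3 to 14 points. The 14-point figure needs 25% against 5% refusal and is an upper-end scenario, not an estimate. If a quarter of decliners would have succeeded, it halves to 7. The two mechanisms can oppose each other, so no net direction can be claimed. Nor does the protocol show that the lottery has failed to protect the main outcome, only that it may not protect it fully. The change is still worth making before the draw, because the order of enrolment cannot be repaired afterwards and a meeting suited to a later draw is already planned.

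**What to change.** 1. **First meeting:** information only, with no draw.
2. **Second meeting:** collect signed forms, record lactating cows and sign each contract, then draw the lottery by concession. Contract at the unit actually used: Section 10.4 refers to the herder responsible for the container, and Section 5 gives about two households per container.
3. **Preferably, draw later still**, once informed consent is signed and the baseline visit is complete. A draw at the second meeting protects the agreement and the contract, but leaves consent and baseline after known allocation, so entry to the anemia comparison stays exposed. A post-baseline draw also keeps enumerators unaware of the arm at baseline.
4. **Text:** amend Summary section 4 and Sections 8 and 10.1 for the new order. In Section 11.1, state that the main outcome is analysed in all households that signed before the draw, in the arm drawn. Report by arm the households lost between draw, consent and baseline.
5. **If the draw cannot move:** have contracts set by someone unaware of the arm, and count every household in the lottery by arm.

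Cost: the second-meeting draw needs protocol wording, a 10-day delay to the draw and less lead time to organise deliveries, but no extra meeting. The post-baseline draw needs a separate way to tell households the result, for example through the milk collectors, and distribution would start slightly later, since baseline and distribution are both planned for January 2013.

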**5. Location and duration**

The study will take place in the department of Dagana, in the area of ​​Richard Toll, amongst farmers of the area supplying milk to the Laiterie du Berger. The study area covers the zones of the Walo and the Diery. The implementation of the "herding" arm of the study (identifying contract objectives for farmers, information meetings etc.) will be entrusted to GRET. The intervention will be coupled with an awareness campaign in the area (the “nutrition” arm). This will cover good dietary practices for children, as well as anemia and means of prevention. It will be led by CLM and its executing partner ASBEF, through their networks of health workers, who are in close contact with the population. The intervention will last 6 months and an evaluation will be conducted at 6 months and 12 months.

# 1. Justification of the study

Current estimates suggest that there are almost 1 billion hungry people in the world (FAO 2010). In sub-Saharan Africa, a substantial share of death and disease results from high levels of undernutrition among mothers and children. Indeed, maternal and child undernutrition has long-lasting, irreversible effects on the development, health, and economic productivity of individuals, communities, and nations. Globally, maternal and child undernutrition is the underlying cause of 3.5 million deaths, 35% of the disease burden in children younger than 5 years, and 11% of total global disability adjusted life years (DALYs) (Black et al. 2009) . Reducing undernutrition is a key factor underpinning the achievement several Millennium Development Goals (MDGs).

Undernutrition encompasses both chronic and acute forms, as well as deficiencies of essential micronutrients. Access to nutrient-rich foods and to diets of adequate quality remains a major impediment towards progress in tackling the problem of undernutrition. Typically, poor households subsist on low-diversity, staple-based diets and lack access to nutritious foods that are rich in essential micronutrients such as vitamin A, iron, and zinc (Ruel et al. 2003; Arimond et al. 2010). Inadequate intake of these micronutrients have far reaching health, nutrition, and developmental consequences both in the short and the long term (Black et al. 2008; MI, 2009). Women of reproductive age and infants and young children are particularly vulnerable to the consequences of micronutrient deficiencies because their life stages correspond with high micronutrient intake requirements (Black et al. 2008; MI, 2009).

A deficit in iron, in its most severe form, leads to iron-deficiency anemia. Due to the facility of measuring hemoglobin levels, the prevalence of anemia has often been used as a proxy for measuring iron-deficiency anemia. This approach is sufficient in areas where iron deficiency is known to be the major cause of anemia. This is not the case in areas where the cause of anemia is much more complex. While it has been estimated that at least 50% of cases of anemia can be attributed to iron deficits (Stoltzfus, 2003), these figures vary considerably depending on the geographic area and age groups concerned. In its latest report on anemia in the world in 2009, the WHO indicates an anemic prevalence among children 0-5 years of 68% in Africa (McLean, 2009). A recent study carried out in Ivory Coast has shown that 40-50% of children and women were anemic and that iron-deficiency anemia was associated with 50% of cases of anemia among school-age children and women, while this figure reached 80% among children of pre-school age (2-5 years) (Staubli, 2001).

High prevalence of anemia in a population is also a reflection of low levels of health. There are many causes of anemia in developing countries. Among them, in addition to iron deficiency, other micronutrients such as folic acid, vitamin B12, and vitamin A appear to be involved. Infectious diseases such as malaria, HIV, and intestinal helminth infections (hookworm and schistosomiasis from Schistosoma haematobium) (Stoltzfus, 2000), as well as hemoglobinopathies (sickle cell disease, thalassemia) (Tolentino, 2007), also play an important role.

The consequences of anemia and iron deficiency on the health of the individual are multiple (Berger, 2002). In adults, they result in a decrease in physical capacity (Gardner, 1977) and productivity (Basta, 1979). In pregnant women, the impact on mortality that is attributable to anemia has been calculated respectively at 6.37, 7.26, and 3.0% respectively for Africa, Asia and Latin America (Brabin, 2001). Anemia and iron deficiency increase the risk of morbidity and fetal and neonatal mortality, of prematurity, and of low infant birthweight (Viteri 1994). In children, iron deficits may cause cognitive dysfunction and affect their development potential (Walker, 2007; Eden, 2005).

Different targeted interventions to provide iron supplements to vulnerable populations have been evaluated (Berger, 2002). Approaches based on increased consumption of iron and food diversity are important strategies for the prevention of iron deficiency and iron-deficiency anemia in the general population. However, integrated approaches that combine supplementation interventions in iron and other health measures (such as deworming, actions to combat malaria, mass treatment for schistosomiasis) were necessary in areas where iron deficiency was not the only cause of anemia. Education and respect for good dietary practices are also essential (Buttha, 2008). Finally, the implementation of interventions in the fight against micronutrient deficiencies (through supplementation, fortification, and dietary modification) should be integrated in agriculture, welfare, and/or health programs (Olney, 2012).

Senegal has seen significant progress in combating malnutrition over the past two decades. Alleviating child malnutrition has been high on the Senegalese policy agenda, with a dedicated unit – the Cellule contre La Malnutrition (CLM) – coordinating major activities in-country and reporting directly to the prime ministers’ office. According to the 2011 DHS report, 83% of children under 5 years and 54% of mothers are anemic in Senegal. According to the same report, growth delays (indicator of chronic malnutrition) affect 27% of children, with thinness or wasting (acute malnutrition indicator) affecting 10% of children and 18% being underweight (DHS 2011).

According to a 2012 report of CLM on the iron status of children aged 12-59 months across Senegal, the prevalence of anemia is 83% for children 12-23 months and declines to 49% for children 48-59 months (MI, 2012). Analyses on iron status indicate that 64.5% of children have an iron deficiency, ranging from 64.3% for children 12-24 months and decreasing to 42.5% for children 48-59 months. Finally, according to the latest Smart 2012 survey, conducted by CLM in the department of Dagana among children 6-59 months, acute malnutrition affected 11.4% of children (as compared to 8.80% nationally), stunting impacted 13.6% (compared to 15.50% nationally), and 15.5% were underweight (compared to 14.50% nationally) (CLM, 2012).

In 2006, the Laiterie du Berger (LDB), a social venture later supported by Danone Communities, Credit Agricole, the Grameen Foundation, and other partners, started to collect milk from pastoralist households living near the town of Richard Toll in the Senegal River Valley. LDB’s business model is to produce high-quality products (primarily yogurt) for mostly urban populations, using fresh milk that it collects itself twice a day from households living within 50 km of its processing plant. Over the years, LDB has built up a reliable base of 700 milk suppliers on 4 main collection routes. At the end of the month, suppliers come to LDB and collect the payment for their month’s production. Part of these payments can be used to purchase discounted animal feeds, which appears to be an important incentive for suppliers. They may also receive an in-kind advance (in animal feeds) of up to 30% of the past month’s production, if they face specific liquidity and/or animal feed needs.

The current study aims to test a type of incentive among farmers to encourage them to provide milk to LDB more regularly during the dry season, while investigating and explaining the mechanisms involved. The incentive will be distributed as a bonus, after a contract with a target volume (corresponding to 1 liter of milk per lactating cow per day) and regularity in the frequency of milk collection has been agreed upon at the beginning of the dry season. The incentive tested will be a dairy product produced by LDB itself: fortified Thiakry. This form of incentive corresponds to the "Value Chain" concept^^[[1]](#footnote-1)^^: the initial product is the milk produced by herders and the processing of the milk produces in yogurt to which millet and fortification are added. This results in a final value-added product (fortified Thiakry) that will be made accessible to herders.

